## Abstract

**Background:**

Varenicline and bupropion are efficacious, prescription-only pharmacotherapies for smoking cessation; however, their real-world impact is limited by prescriber knowledge, affordability, and accessibility.

**Objective:**

The primary objective of the MATCH (Medication Aids for Tobacco Cessation Health) study was to evaluate the real-world, long-term effectiveness of mailed bupropion and varenicline in a sample of interested smokers with the utilization of Web-based recruitment and follow-up. In addition, the study aims to investigate the genotypic and phenotypic predictors of cessation.

**Methods:**

This is a two-group, parallel block, randomized (1:1) open-label clinical trial. This study will be conducted online with the baseline enrollment through the study’s website and follow-up by emails. In addition, medication prescriptions will be filled by the study contract pharmacy and couriered to participants. Individuals who smoke ≥10 cigarettes per day and intend to quit within the next 30 days will be recruited through Public Health Units and Tobacco Control Area Networks throughout Ontario by word-of-mouth and the internet. Eligible participants will receive an email with a prescription for 12-week assigned medication and a letter to take to their physician. The recruitment and randomization will continue until 500 participants per arm have received medication. All participants will receive weekly motivational emails during the treatment phase. The primary outcome measure is the smoking status after 6 months, biochemically confirmed by mailed-in salivary cotinine. Follow-ups will be conducted through emails after 4, 8, 12, 26, and 52 weeks of starting the treatment to assess the smoking prevalence and continuous smoking abstinence. In addition, mailed-in saliva samples will be used for genetic and nicotine metabolism analyses. Furthermore, personality characteristics will be assessed using the Big Five Aspect Scales.

**Results:**

The project was funded in 2014 and enrollment was completed in January 2017. Data analysis is currently underway.

**Conclusions:**

To the best of our knowledge, this is the first randomized controlled trial to mass distribute prescription medications for smoking cessation. We expect this method to be logistically feasible and cost effective with quit outcomes that are comparable to published clinical trials.

**Trial Registration:**

ClinicalTrials.gov NCT02146911; https://clinicaltrials.gov/ct2/show/NCT02146911 (Archived by WebCite at http://www.webcitation.org/72CZ6AvXZ)

**Registered Report Identifier:**

RR1-10.2196/10826

## Introduction

### Background

The prevalence of tobacco smoking in developed countries has steadily declined over the past three decades. However, with 16% of the general Canadian population aged ≥15 years [1], the prevalence of smoking remains a formidable cause of mortality and morbidity in Canada. The burden of tobacco use is high, resulting in Can $17 billion in direct and indirect costs to the Canadian economy [2]. Clinical interventions are an important component of comprehensive tobacco control strategies [3]. Nicotine replacement therapy, bupropion, and varenicline are proven to be efficacious pharmacological aids, doubling the chances of success in quitting smoking [4-6].

To date, 3 randomized controlled trials (RCTs) have compared varenicline, bupropion, and placebo [6-8]. The primary outcome measure was continuous abstinence rates (CARs) at various time points as follows: weeks 9-12 (end of treatment), weeks 9-24 (6-month time point), and weeks 9-52 (1-year time point). Only one trial reported a significant difference in CARs after 52 weeks [7] with varenicline having significantly higher long-term abstinence rates than bupropion (23% vs 14.6%, respectively; odds ratio [OR] 1.77, 95% CI 1.19-2.63, *P*=.004). However, an identical clinical trial conducted in parallel with the same sample size [6] did not show a significant difference in CARs between varenicline (21.9%) and bupropion (16.1%; OR 1.46, 95% CI 0.99-2.17, *P*=.06) after 52 weeks.

Therefore, although there is limited evidence for the superior long-term efficacy of varenicline, no study has assessed the real-world effectiveness of these medications for long-term abstinence. This is important because of some significant differences between clinical trials and real-world settings, which could influence cessation treatment outcomes; for example, clinical trials have strict eligibility criteria, excluding participants with certain comorbidities. Therefore, participants in these studies are in better health compared with the general population. In addition, treatment with medications in clinical trials is accompanied by one-on-one smoking cessation behavioral counseling often on a weekly basis, which is largely unavailable in real-world settings [7]. These factors together have the potential to restrict the external validity of clinical trial findings. As such, there is a need to assess the real-world effectiveness of these prescription medications at a population level to further strengthen the evidence base for the effective treatment of tobacco dependence.

Even though proven efficacious in clinical trials, according to the Canadian Tobacco Use Monitoring Survey in 2007, less than half of smokers who have ever attempted to quit have used a smoking cessation aid [9]. Most of these smokers identify the lack of access to adequate and evidence-based information, in addition to the cost, as reasons for not using these smoking cessation pharmacotherapies [9]. Furthermore, bupropion and varenicline are only available by a prescription from a licensed practitioner. Therefore, in addition to knowledge and affordability, their population-level impact is limited by accessibility. Furthermore, smoking cessation clinics are limited in number, and a survey conducted in Canada demonstrated that the occurrence of smoking cessation discussion between physicians and patients is not common. In fact, of 88% of smokers who visited a primary care physician in the year prior, only half received any advice on quitting or reducing smoking [10]. Efforts to address these barriers could greatly improve the use and effectiveness of these smoking cessation medications in real-world settings [11]. Furthermore, mass distribution approaches, bypassing clinics and physicians, have been successful for nicotine replacement therapy [12,13]. However, bupropion and varenicline have the potential to make a greater impact, given their superior results from clinical trials.

### Study Aims

The primary aim of this large RCT is to assess the long-term cessation rates associated with bupropion and varenicline treatment using the internet as a novel approach. Secondary aims include investigating the pharmacogenetic factors and phenotypic characteristics affecting nicotine dependence and smoking cessation outcomes.

### Hypotheses

The hyphotheses of the study are as follows: the long-term abstinence rates (at 6-month follow-up) will be significantly higher in the varenicline group than in the bupropion group; the overall quit rates will be similar to those reported from traditional RCTs; and specific genotypes and phenotypes of individuals will influence smoking treatment outcomes.

## Methods

### Study Design

The Medication Aids for Tobacco Cessation Health (MATCH) study is an internet-based pragmatic randomized clinical trial. This study is open-label, wherein eligible participants are randomly assigned to study medication, bupropion (Zyban) or varenicline (Champix), for 12 weeks in conjunction with weekly motivational emails. All participants will receive medication plus an identical email-based behavioral intervention. The research methods and protocol for this study have been approved by the standing Research Ethics Board (REB) at the Centre for Addiction and Mental Health (CAMH) with the reference number 200/2012. This study is registered at ClinicalTrials.gov (NCT02146911). Figure 1 shows a CONSORT (Consolidated Standards of Reporting Trials) diagram for the study outlining estimates for the recruitment and dropout. The figure illustrates the estimated participant flow of the proposed intervention trial. It demonstrates the expected participant numbers in the enrollment and study completion processes. The estimated number of participants active at each stage of the study are estimated based on the pilot study conducted previously [14].

### Setting

#### Web-Based Consent, Self-Assessment, and Automated Eligibility Determination

Figure 2 shows the flowchart of participants through different components of the study. It includes the enrollment process, followed by randomization, mailing of the medication, and follow-up surveys completed at various time points.

Interested individuals will visit the study website and read a brief description of the study purpose, its procedures, and treatments provided. Those interested in participating will read the study information and consent form and provide their consent by clicking “yes” on the study website; they may also indicate whether they would like to be contacted for future studies. Individuals are permitted to participate in the study even if they do not give consent to be contacted for future studies. After completing the consent form, participants will complete the baseline survey, which will take approximately 20 minutes. The baseline questionnaire collects information on demographics, socioeconomic factors, education, ethnicity, smoking habits (cigarettes smoked per day, duration of daily smoking, and when participants first began smoking), importance and confidence to quit, substance and alcohol usage, concurrent usage of other medication(s), and any psychiatric comorbidities (ie, depression, anxiety, and schizophrenia).

In addition, if eligible, participants will be asked if they consent to provide a saliva sample for the genetic testing component of the study. If they agree to enroll in this substudy, they will complete the Big Five Aspect Scale personality test online through the study website, which will take approximately 10-15 minutes. Big Five Aspect Scale is a self-reported public domain test, which assesses the big 5 personality traits by asking 100 questions answered on a 5-point scale ranging from “strongly disagree” to “strongly agree” [14]. Individuals will be permitted to take part in the efficacy study even if they do not consent to participation in the genetics substudy. The questionnaires used have been published previously and include the Fagerstrom test for nicotine dependence [15], the BFAs for accessing the big 5 personality traits—extraversion, neuroticism, conscientiousness, agreeableness, and openness to experience [14]—and Patient Health Questionnaire for the evaluation of depression [16]. These questionnaires have been widely used in clinical studies, involving smoking, and extensively validated [14-16].

**Figure 1 figure1:**
[figure not shown]
An overview of the proposed intervention trial (CONSORT [Consolidated Standards of Reporting Trials] diagram).

**Figure 2 figure2:**
[figure not shown]
Participants’ flowchart. BFAS: Big Five Aspect Scale.

After submitting the completed questionnaires, individuals will be notified, through an on-screen message, whether they are eligible for the study. Those who are eligible will receive an email, including their medication assignment, the study information and consent form, a standardized letter to the doctor to convey information about the study, and a standard script for the study medication they have been assigned to for their physician (or other licensed prescriber) to sign. Because there are no in-person study visits, Salivette kits will be mailed out at the time of study enrollment to verify the participants’ smoking status.

In addition, baseline saliva sample will be used to measure the nicotine metabolite ratio, which is the ratio of 3'-hydroxycotinine and cotinine (COT) concentration; this is a validated phenotypic biomarker of the CYP2A6 enzyme activity [17]. Furthermore, Salivette kits will be sent at weeks 4, 26, and 52 to measure the salivary COT level for the biochemical verification of abstinence. Those who consent to the genetics substudy will receive a second email with the genetics study information and consent form and the Oragene saliva DNA kits by mail to collect a DNA sample for the pharmacogenetics component of the study. Participants will be compensated for each DNA (if applicable) and subsequent saliva samples received.

#### Patient Visit to a Licensed Practitioner

All eligible participants will be required to visit their physician or another licensed prescriber within 5 weeks from the enrollment date to sign the prescription for their assigned medication. Reminder emails will be sent after 2 weeks of the enrollment date to make sure that the participants have booked an appointment to visit their practitioner. At the visit, participants will discuss their medical history, the medications they are on, and any other concerns they have regarding the treatment. At his or her discretion, a licensed practitioner may either sign the prescription for study medication or choose not to prescribe the assigned medication to their patient. The practitioner’s office will then fax the signed prescription to a mail-order pharmacy contracted to do the study that will then fill the prescription.

#### Mail-Out Pharmacy

Prescriptions signed by a licensed practitioner and verified to be authentic will be filled and mailed to the participants’ addresses by the contract mail-order pharmacy. In accordance with the Ontario College of Pharmacists’ standard of practice, pharmacists will call each study participant at the time of dispensing (ie, mailing) the medication to inform participants about directions to use the medication, discuss possible allergies, concomitant medications, and offer counseling.

### Participants

#### Inclusion and Exclusion Criteria

The following inclusion criteria will need to be met before any individual is randomly assigned to one of the 2 treatment arms: Ontario resident; having a valid email address; aged at least 19 years; current daily smoker; smoking at least 10 cigarettes per day; smoked daily for at least the past year; and have an intention to quit smoking within 30 days of receiving the medication. The following are criteria that will exclude an individual from being randomly assigned to one of the 2 treatment arms: a history of psychotic disorder (schizophrenia or bipolar disorder) or eating disorder; brain injury; seizure disorder; pregnancy, lactation, or at risk of becoming pregnant; allergy or sensitivity to bupropion or varenicline; or currently taking varenicline or Champix, bupropion or Zyban or Wellbutrin, monoamine oxidase inhibitors, thioridazine, antidepressants, or other medications containing bupropion hydrochloride.

#### Recruitment and Randomization

The primary method of recruitment for this study will be by word-of-mouth through family, friends, or health care providers. The Smoking Treatment for Ontario Patients Study [12,13], also conducted by the investigators of this trial, has successfully built a collaborative network of providers from public health units, community health centers, family health teams, and community pharmacies across Ontario. This network of providers has proven to be effective in disseminating new treatment opportunities to smokers in their area. Interested individuals will self-identify and will be directed to enroll through the study website. Moreover, as part of the consenting procedure for those who participated in the Smoking Treatment for Ontario Patients Program, individuals will be asked whether they would like to be contacted about new research opportunities by CAMH. Those who choose “yes” will then be included in a database forming a smokers’ registry that can be contacted in case new research opportunities come up. This smokers’ registry will be another method of recruitment used for this study. Furthermore, the public will be informed about the study through CAMH social media accounts, Smokers’ Helpline, and Facebook advertisements.

#### Randomization

Eligible participants will be randomly assigned to one of the 2 study arms (varenicline or bupropion). Permuted block randomization in a 1:1 ratio in blocks of 100 will be employed. The randomization process will be computerized. Owing to the large proposed sample size in this study, there will be no stratification or minimization.

#### Current Recruitment Status

Study recruitment is no longer active; however, there are still few 1-year follow-ups that are yet to be completed by participants.

#### Retention Strategies

Weekly motivational emails and payment for mailed-in saliva samples at the 4-week time point will be used to encourage treatment fidelity and maintain engagement in the study.

#### Sample Size

In the 2 head-to-head RCTs of varenicline versus bupropion [6,7], participants were randomized 1:1:1 to varenicline, bupropion, or placebo arms with 341-345 participants in each group. In the trial conducted by Gonzales et al [6], the 9- to 52-week CARs were 21.9% in the varenicline group versus 16.1% in the bupropion group (OR 1.49, 95% CI 0.99-2.17, *P*=.057). In the trial conducted by Jorenby et al [7], the 9- to 52-week CARs were 23% in the varenicline group compared with 14.6% in the bupropion group (OR 1.77, 95% CI 1.19-2.63; *P*=.004). Because this is an effectiveness trial, we anticipate lower quit rates overall. Indeed, in our previous feasibility study [18], 7-day point prevalence abstinence (PPA) rates after 6 months (intention-to-treat analysis) were 18.9% in those who received varenicline and 17.4% in those who received bupropion.

To be sufficiently powered to detect a significant difference in the 26-week CARs, we plan to randomize 500 subjects to each medication arm. We predict that the real-world abstinence rates will be slightly lower than those observed in clinical trials and may be similar to what we found in our nonrandomized study that this protocol is based on [19]. Therefore, we assumed that the 26-week CAR in the varenicline-treated group would be 20% compared with 15% in the bupropion-treated group. At 500 subjects per group, we will have 80% power to detect a significant difference between groups at a .05 level of significance.

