### Primary Outcome

The primary outcome measures will be related to the effectiveness of treatment. The primary outcome will biochemically confirm 30-day continuous abstinence by mailed-in salivary COT 26 weeks after the start of treatment. Secondary outcome variables will be self-reported 30-day continuous abstinence at the end of the treatment (weeks 9-12) and at weeks 26 and 52; this is defined as not having smoked, even a puff, in the past 30 days and lack of relapse during this period. Other outcome variables include self-reported 7-day PPA measured at weeks 4, 8, 12, 26, and 52. The 7-day PPA is defined as not having smoked, even a puff, over the last 7 days.

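### The 80% power claim is made for a 26-week continuous abstinence rate, not for the cotinine-confirmed 30-day primary outcome, and no two-sided scenario tested for that outcome reaches 80%

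*Protocol article*

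**What the plan says.** Three parts of the protocol article bear on this point.

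- **Sample Size.** The target is set "To be sufficiently powered to detect a significant difference in the 26-week CARs". The planning rates are given as "we assumed that the 26-week CAR in the varenicline-treated group would be 20% compared with 15% in the bupropion-treated group", followed by "At 500 subjects per group, we will have 80% power to detect a significant difference between groups at a .05 level of significance". The section leads up to these rates with week 9 to 52 CARs from two head-to-head trials (21.9% vs 16.1%, and 23% vs 14.6%) and with 7-day point prevalence at 6 months from a feasibility study (18.9% vs 17.4%).
- **Primary Outcome.** "The primary outcome will biochemically confirm 30-day continuous abstinence by mailed-in salivary COT 26 weeks after the start of treatment". The 30-day measure is defined as "not having smoked, even a puff, in the past 30 days and lack of relapse during this period".
- **Data Analysis.** Anyone lost to follow-up, or without a saliva sample for cotinine confirmation, is counted as a smoker.

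The Background section describes the CARs of the earlier trials as covering weeks 9-12, 9-24 and 9-52. The Hypotheses section expects that "the overall quit rates will be similar to those reported from traditional RCTs", and the Abstract's conclusions say much the same.

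**The concern.** The power statement and the primary analysis concern different quantities. A CAR, as the article uses the term for the earlier trials, requires abstinence from week 9 onwards. The primary outcome looks back 30 days from week 26 and also requires a posted sample. Rates argued from week 9 to 52 CARs and 7-day point prevalence are not rates for that outcome, and the sample-size text does not convert them.

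Two things are at stake. First, a reader who trusts the 80% could take a non-significant primary result as evidence that the drugs differ little, when the trial may have had much less chance of detecting the planned difference. Second, if 30-day quit rates come out close to the earlier trials' CARs, this could be reported as confirming the hypothesis of similarity although the two outcomes are defined differently.

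**Working it through.** **Inputs.** From Sample Size: 20% and 15%, n=500 per arm, alpha 0.05, sidedness not stated. From Randomization: 1:1 allocation. The text gives no saliva-return rate, so r, the share of abstainers who return a sample, is an assumption. It is taken as equal in both arms.

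**Formula.** For two proportions a and b with mean m:

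power = Φ{[(a − b) − z·s0] / s1}, where s0 = √[2m(1 − m)/n] and s1 = √{[a(1 − a) + b(1 − b)]/n}.

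**Step 1: the plan's own figure.** With a=0.20, b=0.15, n=500: s0 = 0.02403 and s1 = 0.02398.

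- Two-sided (z=1.960): (0.05 − 0.04710)/0.02398 = 0.121, so power is 55%.
- One-sided (z=1.645): (0.05 − 0.03953)/0.02398 = 0.437, so power is 67%.

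Unpooled and arcsine versions also give 55% two-sided; a continuity correction gives 51%. The stated 80% does not reproduce. It would need 906 per arm two-sided, or 714 one-sided. This error exists before any question of endpoint arises.

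**Step 2: non-return scored as smoking.** Treat 20% and 15% as true abstinence and multiply both by r (n=500, two-sided):

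| r | Rates | Power | n per arm for 80% |
|---|---|---|---|
| 1.0 | 20.0% vs 15.0% | 55% | 906 |
| 0.9 | 18.0% vs 13.5% | 50% | 1028 |
| 0.8 | 16.0% vs 12.0% | 44% | 1181 |
| 0.7 | 14.0% vs 10.5% | 39% | 1377 |
| 0.6 | 12.0% vs 9.0% | 34% | 1638 |
| 0.5 | 10.0% vs 7.5% | 29% | 2005 |

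**Step 3: the shorter window.** A 30-day look-back is easier to satisfy than abstinence from week 9, so rates could be higher. Hold the planned odds ratio, (0.20/0.80)/(0.15/0.85) = 1.42, and raise the bupropion rate (an assumption), with full return:

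- Bupropion 20%: odds 0.25 × 1.4167 = 0.354, so varenicline is 26.2%. Power is 64% (735 per arm for 80%).
- Bupropion 25%: odds 0.333 × 1.4167 = 0.472, so varenicline is 32.1%. Power is 70% (639 per arm for 80%).

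**Step 4: both effects together.** Starting from 26.2% vs 20%, r=0.9 gives 23.5% vs 18.0% and power 58%, above the 55% of step 1. At r=0.7 it gives 18.3% vs 14.0% and power 46%, below it. The sign of the net effect therefore depends on two quantities that the text does not give.

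**The case against.** The best defence is that 26-week CAR is loose shorthand. The primary outcome is itself called 30-day continuous abstinence, and the abbreviation list expands CAR without a time window. On that reading only the label is untidy. This is possible, but Sample Size uses CAR for week 9 to 52 abstinence just before it states the planning rates, and the shorthand reading still leaves no stated allowance for saliva return.

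A second defence is that 20% and 15% are rounded judgements, and that the feasibility rates were intention-to-treat and so may already count some non-responders as smokers. This stands as a caution: multiplying by r assumes that the planning rates are true abstinence, which the text does not say. Figure 1, described under Study Design as giving recruitment and dropout estimates, is not available here, so it cannot be said that the plan has no dropout assumption. What can be said is that the sample-size text states none.

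Some stronger readings are tempting but not supported:

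- **That the endpoint mismatch lowers power.** Step 4 shows that it can go either way. Setting 50% at r=0.9 against the stated 80% would also blame the endpoint for the arithmetic error; the return effect there is about 5 points, from 55% to 50%.
- **That the article contradicts itself on quit rates.** "Because this is an effectiveness trial, we anticipate lower quit rates overall" sits awkwardly beside the similarity hypothesis, but the same section then says only slightly lower, and the two can coexist. No formal test against the earlier trials is planned.
- **That the weeks between the week-12 and week-26 look-backs are a data gap.** The article lists no week 9 to 26 outcome, so nothing it plans depends on them.
- **That the medicated-only analysis set adds to this mismatch.** Sample Size also speaks of treated participants, so the choice of denominator is a separate question.

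**Conclusion.** The concern holds in this form: the power claim is attached to an outcome that is not the primary outcome, its rates are not justified for the primary outcome, and the sample-size text has no stated allowance for samples that do not come back. The direction of the resulting error in the rates is undetermined.

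In the two-sided scenarios above, power runs from 29% to 70%. Of the shortfall from 80%, about 25 points (80% to 55%) come from arithmetic on the plan's own inputs and have nothing to do with the endpoint. The r values and the raised 30-day rates are illustrations, not estimates.

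A one-sided reading does not rescue the claim at the planning rates (67%). One-sided power passes 80% (83%) only when the bupropion rate is taken to be 30%, twice the planned value, against 37.8% with full sample return.

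For the comparison with earlier trials, the conclusion is only that 30-day abstinence and a week-9-onward CAR are different measures. The article does not say whether the earlier CARs were biochemically verified, so nothing here rests on that.

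**What to change.** In Sample Size, replace the 26-week CAR with the outcome defined under Primary Outcome. State the assumed rates for that outcome in each arm, with an explicit saliva-return assumption and non-return scored as smoking. State whether the test is one- or two-sided, and give the power as recomputed, which will be below 80% in the two-sided scenarios shown here.

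Where the Hypotheses section and the Abstract's conclusions set quit rates beside earlier trials, call the comparison descriptive and say that 30-day abstinence is not a week-9-onward CAR.

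The cost is wording and a less favourable power figure; no new data are needed. Enrolment closed in January 2017, so the change cannot alter the sample size. It can still govern how a non-significant primary result and the comparison with earlier trials are read, since the article describes the analysis as under way and first results as not yet submitted.

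### The stated 80% power does not follow from the plan's own inputs: 20% versus 15% with 500 per arm gives about 55% two-sided, and 67% at best one-sided

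*Protocol article*

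**What the plan says.** The Sample Size section of the protocol article gives every input to the calculation. On the rates: "we assumed that the 26-week CAR in the varenicline-treated group would be 20% compared with 15% in the bupropion-treated group". On the numbers: "we plan to randomize 500 subjects to each medication arm". The conclusion is: "At 500 subjects per group, we will have 80% power to detect a significant difference between groups at a .05 level of significance". Sidedness is not given, and neither is the formula.

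Three other places bear on the calculation:
- **Allocation** is 1:1 (Randomization).
- **Number analysed.** The abstract's Methods say "The recruitment and randomization will continue until 500 participants per arm have received medication". The Data Analysis section analyses those who were randomized and received their medication, and counts missing follow-up or a missing saliva sample as smoking.
- **Direction.** The first hypothesis is that 6-month abstinence "will be significantly higher in the varenicline group than in the bupropion group".

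**The concern.** A difference of 5 points from a base of 15% is small for a two-arm trial of 1,000 people, and 80% power looked too high on sight. This is the power for the trial's main comparison and the only justification offered for its size.

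If true power is well below 80%, a non-significant result says much less than the protocol implies. A reader who takes 80% at face value would regard a null finding as fair evidence that varenicline has no advantage of the assumed size. At the real power, such a finding would be close to a coin toss even if the assumption were exactly right.

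**Working it through.** **Inputs** (Sample Size): p1 = 0.20, p2 = 0.15, difference 0.05, n = 500 per arm, α = .05. No allowance for dropout is needed, because missing counts as smoking and recruitment runs until 500 per arm have received medication.

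**Attempt to reproduce 80%, two-sided z test with pooled null variance**
- Mean rate: (0.20 + 0.15)/2 = 0.175.
- SE under the null: √(0.175 × 0.825 × 2/500) = 0.02403.
- SE under the alternative: √(0.20 × 0.80/500 + 0.15 × 0.85/500) = 0.02398.
- Power = Φ[(0.05 − 1.960 × 0.02403)/0.02398] = Φ(0.121) = **54.8%**.

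**One-sided .05**
- Power = Φ[(0.05 − 1.645 × 0.02403)/0.02398] = Φ(0.437) = **66.9%**.

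**Other methods, same inputs**

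| Method | Two-sided .05 | One-sided .05 |
|---|---|---|
| Pooled variance | 54.8% | 66.9% |
| Unpooled variance | 55.0% | 67.0% |
| Arcsine | 55.0% | 67.0% |
| Log odds ratio | 54.6% | 66.6% |
| Exact power of the chi-square test | 54.8% | 67.1% |
| Continuity-corrected | 51.5% | 63.8% |

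A simulation of 400,000 trials with the two-sided chi-square test gave 54.9%. Even a one-sided test at .10 (two-sided .20), which the protocol does not mention, gives only 78.8%. The stated figure is not reproduced by any of these.

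**Sample size that 80% power needs**
- Two-sided: n = [1.960 × √(2 × 0.175 × 0.825) + 0.842 × √(0.20 × 0.80 + 0.15 × 0.85)]² / 0.05² = 905.4, so **906 per arm** (1,812 in total; 945 per arm with continuity correction).
- One-sided: 713.04, so 714 per arm (753 with continuity correction).
- 906/500 = 1.8 times the planned size.

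**What 500 per arm can detect**, with 15% on bupropion, two-sided .05: power is 78.8% at 21.75% on varenicline and 81.4% at 22.0%. The 80% point lies at about **21.9%**, a difference of 6.9 points rather than 5.

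**Precision.** The expected 95% CI half-width for the risk difference is 1.96 × 0.02398 = 0.047, or 4.7 points, nearly as wide as the assumed effect.

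**Other rates in the same section**, at 500 per arm, two-sided .05. These are different endpoints or time points and serve only to show sensitivity:
- 21.9% versus 16.1%: 64.8%.
- 23% versus 14.6%: 92.6%.
- The feasibility study's 18.9% versus 17.4%: 8.9%.

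**The case against.** Four points can be made on the other side.

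- **Sidedness is not stated and the hypothesis is directional.** This is fair. The 45% miss rate and the coin-toss description belong to the two-sided reading; one-sided, the miss rate is about 33%. Both readings fall short of 80%, by about 25 and 13 points.
- **The planned longitudinal GEE model could add precision.** Suppose a constant 5-point difference were averaged over all five follow-ups with a common within-person correlation ρ. The effective sample per arm is then 500 × 5/(1 + 4ρ), which reaches 906 at ρ of about 0.44. That would be the power for an average over visits. The Sample Size section ties its figure to the 26-week rates, and the protocol gives no correlation. The point does mean that the 55% should be described as the power of the 26-week comparison.
- **The wrong number may be the rates, not the power.** Averaging the two cited trials gives (21.9 + 23)/2 = 22.45% and (16.1 + 14.6)/2 = 15.35%, for which 500 per arm has 81.9% power. The 500 and the 80% may have come from rates like these. The protocol does not say so, and it expressly assumes 20% and 15%. Whatever the origin, the sentence as written is wrong.
- **Enrolment is complete, so nothing but wording can change.** This is true, and no passage says that a null result will be read as equal effectiveness. The observed confidence interval will show the precision in any case. The stated power is still what a reader would use to weigh a non-significant result, and it is wrong for the main comparison.

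**Conclusion.** The concern holds. With the plan's own rates, sample size and significance level, power is about 55% two-sided, and no more than about 67% if a one-sided .05 test was meant. The type II error is about 45% (33% one-sided), against the 20% implied. The conclusion rests on a comparison of two proportions at 26 weeks with 500 analysed per arm. If 500 were only randomized and fewer received medication, power under the same rates would be lower still. Dropout, choice of formula and the planned GEE do not account for the discrepancy. Because the error concerns the primary comparison and can be settled from one paragraph, it must be corrected.

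**What to change.** Replace the power sentence with wording such as: *For the 26-week comparison of two proportions, 500 participants per arm give about 55% power (two-sided .05) for 20% versus 15%, and 80% power for about 22% versus 15%.* State the sidedness and the formula. If the 80% came from other rates or from a repeated-measures calculation, give those inputs and reconcile them with the 20% and 15% now stated.

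It would also help to report the risk difference with its 95% CI and to say that a non-significant p value will not be read as equal effectiveness. The arithmetic does not require this, and it would need to be squared with the logistic GEE in the Data Analysis section.

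The cost of the correction is wording and a less favourable stated power. It needs no further participants and changes neither the data nor the type I error.
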